## LIST OF ABBREVIATIONS

|                 |                                                                  |
|-----------------|------------------------------------------------------------------|
| AE              | Adverse Event                                                    |
| AR              | Adverse Reaction                                                 |
| AUC             | Area Under Curve                                                 |
| $\alpha$ -cells | Alpha-cells                                                      |
| $\beta$ hCG     | beta human Chorionic Gonadotrophin                               |
| CGM             | Continuous Glucose Monitor                                       |
| CI              | Chief Investigator                                               |
| CRA             | Clinical Research Associate (Monitor)                            |
| CRF             | Case Report Form                                                 |
| CRO             | Contract Research Organisation                                   |
| CRU             | Clinical Research Unit                                           |
| CT              | Clinical Trials                                                  |
| CTA             | Clinical Trials Authorisation                                    |
| DBP             | Diastolic Blood Pressure                                         |
| DEPTH           | Dapagliflozin during Exercise for the PrevenTion of Hypos        |
| DM              | Diabetes Mellitus                                                |
| DMC/DMSC        | Data Monitoring Committee / Data Monitoring and Safety Committee |
| DSUR            | Development Safety Update Report                                 |
| DTU             | Diabetes Trials Unit                                             |
| $\delta$ -cells | Delta-cells                                                      |
| EPR             | Electronic Patient Record                                        |
| eTMF            | Electronic Trial Master File                                     |
| FGM             | Flash Glucose Monitoring                                         |
| GCP             | Good Clinical Practice                                           |
| GP              | General Practitioner                                             |
| HRA             | Health Research Authority                                        |
| HTA             | Human Tissue Authority                                           |
| ICF             | Informed Consent Form                                            |
| ICH             | International Council for Harmonisation                          |
| IMP             | Investigational Medicinal Product                                |
| IRB             | Independent Review Board                                         |
| KATP            | ATP-sensitive Potassium channel                                  |

---

|           |                                                                                                |
|-----------|------------------------------------------------------------------------------------------------|
| LEGEND-A  | Low-dose Glibenclamide in Diabetes – Part A                                                    |
| LEGEND-D  | Low-dose Glibenclamide and Dapagliflozin in type 1 Diabetes                                    |
| MHRA      | Medicines and Healthcare products Regulatory Agency                                            |
| mmol/mol  | millimoles per mole                                                                            |
| ng/ml     | nanograms per millilitre                                                                       |
| NHS       | National Health Service                                                                        |
| Non-DM    | Without diabetes                                                                               |
| RES       | Research Ethics Service                                                                        |
| RGEA      | Research Governance, Ethics and Assurance                                                      |
| OCDEM     | Oxford Centre for Diabetes, Endocrinology and Metabolism                                       |
| OUH       | Oxford University Hospitals                                                                    |
| pmol      | Picomoles                                                                                      |
| PI        | Principal Investigator                                                                         |
| PIL       | Participant/ Patient Information Leaflet                                                       |
| POC       | Point of Care                                                                                  |
| R&D       | NHS Trust R&D Department                                                                       |
| REC       | Research Ethics Committee                                                                      |
| RSI       | Reference Safety Information                                                                   |
| SAE       | Serious Adverse Event                                                                          |
| SAR       | Serious Adverse Reaction                                                                       |
| SBP       | Systolic Blood Pressure                                                                        |
| SDV       | Source Data Verification                                                                       |
| SGLT2i    | Sodium-glucose co-transporter 2 inhibitor                                                      |
| SMG       | Statistics and Modelling Group                                                                 |
| SmPC      | Summary of Medicinal Product Characteristics                                                   |
| SOP       | Standard Operating Procedure                                                                   |
| SUSAR     | Suspected Unexpected Serious Adverse Reactions                                                 |
| $t_{1/2}$ | half-life                                                                                      |
| TEAE      | Treatment Emergent Adverse Events                                                              |
| T1D       | Type 1 Diabetes                                                                                |
| TMF       | Trial Master File                                                                              |
| TSG       | Oxford University Hospitals NHS Foundation Trust / University of
Oxford Trials Safety Group |
| USAN      | United States Adopted Name                                                                     |

## 1 Introduction

Type 1 diabetes (T1D) affects around 400,000 people in the UK and is caused by nearly complete loss of insulin-producing cells in the pancreas. It is often challenging to achieve good control of blood glucose throughout the day in T1D, in part because of fluctuations associated with giving insulin. Severe episodes of low blood sugar levels, commonly called “hypos”, are one of the most feared complications of managing diabetes with insulin.

The impaired release of other hormones, such as plasma glucagon which raises blood sugar, during hypo episodes is also part of type 1 diabetes. A better understanding of this mechanism could lead to treatments aimed at reducing the risk of hypoglycaemia.

Glibenclamide is an oral anti-diabetic medication (sulfonylurea) which is commonly used to increase the amount of insulin released by the pancreatic beta-cells. Recent pre-clinical studies have shown that sulfonylureas can also improve plasma glucagon levels when used in very small doses by working on pancreatic alpha-cells, which release plasma glucagon. We have previously conducted a pilot study (LEGEND-A), which suggested that low doses of glibenclamide (0.3mg/day) could alter plasma glucagon release in some people with type 2 diabetes without increasing the risk of hypoglycaemia. In addition, another type of oral anti-diabetic medication, called dapagliflozin, has also been shown to work on pancreatic alpha-cells.

Therefore, the aim of this follow-up study (LEGEND-D) is to find out whether similar doses of glibenclamide or a single dose of dapagliflozin could increase plasma glucagon release in people with T1D. We hope that add-on therapies such as these may become a new way of helping people with T1D to prevent hypoglycaemia.

The trial will involve 2 groups of participants:

- a) 20 people with T1D, who will be given a liquid form of glibenclamide orally for a maximum of 54 days (at 3 different doses, in 3 blocks of 14-18 days), followed by a single oral dose of dapagliflozin, and undergo 5 controlled hypoglycaemia challenges.
- b) A control group of 10 people without diabetes, who will undergo one hypoglycaemia challenge without receiving any medication.

During these challenges, we will gradually drop participants' blood sugar from a normal level (around 6 mmol/L) to a lower level (around 2.5mmol/L) for 40 minutes. While this is a well-established procedure, this change in blood sugar can be stressful and participants without diabetes will probably not have experienced the symptoms before. We will screen all participants for high risk conditions, and monitor them closely during

the entire procedure. We will use a continuous glucose monitor during the study in participants with T1D. All participants will need to attend the OCDEM Clinical Research Unit at the Churchill Hospital, Oxford for an initial screening visit. This will be followed by 8 study visits over a period of 8-10 weeks (divided into around 2-week blocks) for the people with T1D, and the people without diabetes will have just 1 study visit.

The purpose of this statistical analysis plan (SAP) is to outline the planned analyses to be performed in the LEGEND-D trial. The SAP will be amended if changes to the planned analyses are required, and will be finalised before the database lock for this study. Exploratory post-hoc or unplanned analyses not necessarily identified in this SAP may be performed on these data as required. These analyses will be clearly identified in the statistical report for the study.

## **1.1 Study Objectives**

### **1.1.1 Primary Objectives**

1. To determine whether treating people with T1D for 14 to 18 days with oral glibenclamide at 0.3mg, 0.6mg or 3mg daily can increase the counter-regulatory plasma glucagon response during induced hypoglycaemia compared to baseline (pre-treatment).

### **1.1.2 Exploratory Objectives**

1. To compare the plasma glucagon response during induced hypoglycaemia in people with T1D prior to glibenclamide treatment, and at each dose step, to that of participants without diabetes (non-DM group).
2. To compare the increase in plasma glucagon from euglycaemia to hypoglycaemia in T1D participants prior to treatment, and at each dose step of glibenclamide, to that of participants without diabetes (non-DM group).
3. To compare the percentage of time spent in hypoglycaemia (

**Table 1)** at each dose step of glibenclamide, compared to baseline (T1D group only)

**Table 1 : Definition of hypoglycaemia**

|                |                                                                                                                       |
|----------------|-----------------------------------------------------------------------------------------------------------------------|
| Level 1 | < 4.0 mmol/L (70mg/dL) = glucose alert                                                                         |
| Level 2 | < 3.0 mmol/L (54mg/dL) = clinically important hypoglycaemia                                                    |
| Level 3 | <4.0 mmol/L with severe cognitive impairment requiring external assistance for recovery = severe hypoglycaemia |

4.To compare the change in plasma glucagon from euglycaemia to hypoglycaemia in T1D participants prior to and following administration of a single 10 mg dose of oral dapagliflozin, to that of participants without diabetes (non-DM group).

5.To compare the change in plasma somatostatin from euglycaemia to hypoglycaemia in T1D participants prior to and following administration of a single dose of dapagliflozin 10mg, to that of participants without diabetes (non-DM group).

6.To characterise the development of hypoglycaemic symptoms during induced hypoglycaemia at baseline, and during each dose of glibenclamide and dapagliflozin.

7.To measure any residual C-peptide participants with T1D only.

### 1.1.3 Safety Objectives

1. To measure the frequency of adverse events in participants treated with Glibenclamide and Dapagliflozin.

## 1.2 Study Design

The LEGEND-D trial is a pilot, randomised cross-over, single-centre, non-blinded, clinical trial which aims to investigate the effect of 3 low doses of glibenclamide (0.3mg, 0.6mg and 3mg/day) assigned in all possible sequences followed by dapagliflozin (single dose of 10mg) on the plasma glucagon response during induced hypoglycaemia in people with type 1 diabetes, compared to non-diabetic individuals (**Figure 1**). The trial will be conducted by the Oxford Centre for Diabetes, Endocrinology and Metabolism (OCDEM) Clinical Research Unit (CRU) at the Churchill Hospital.

**Figure 1:** Trial flow chart

[figure not shown]

A summary timeline of the trial is shown on figure 1 above. For participants with T1D, the trial is divided into 5 steps, and involves 5 hyperinsulinaemic hypoglycaemic clamps. Once step 1 (no medication) has been completed, the participants with T1D will be randomised to a sequence of glibenclamide doses for the subsequent steps, followed by a single dose of 10mg dapagliflozin. There will be a washout phase of at least 48 hours between each step (the half-life of the glibenclamide suspension is 8 hours) [1]. Participants without diabetes will undergo a single hyperinsulinaemic hypoglycaemic clamp, as they will not receive any study medication.

The total daily dose as defined by the dosing schedule will be split into AM and PM as shown in

**Table 2.**

**Table 2 : Oral glibenclamide suspension doses and volumes**

| Total dose | Strength | AM     | PM            | Total volume over 14 days (min) | Total volume over 18 days (max) |
|------------|----------|--------|---------------|---------------------------------|---------------------------------|
| 0.3mg      | 0.6mg/ml | 0.25ml | 0.25ml        | 7ml                             | 9ml                             |
| 0.6mg      | 0.6mg/ml | 0.5ml  | 0.5ml         | 14ml                            | 18ml                            |
| 3mg        | 0.6mg/ml | 2.5ml  | 2.5ml         | 70ml                            | 90ml                            |
|            |          |        | Total: | 91ml                     | 117ml                    |

As mentioned above, for participants with T1D the final hyperinsulinaemic hypoglycaemic clamp will involve them taking a single dose of dapagliflozin 10mg orally at the start of the study visit.

The main pharmacologically relevant site of action of dapagliflozin (Forxiga, AstraZeneca), is the sodium-glucose cotransporter 2 in the proximal convoluted tubules of the kidneys. By inhibiting this transporter, the threshold for glucose reabsorption is reduced, leading to increased glucose excretion.

Dapagliflozin also leads to increased plasma glucagon secretion by acting directly on the pancreatic islet cells [2]. Plasma glucagon concentrations are increased compared to baseline 2 hour after dapagliflozin administration, and reach a peak of 79pg/ml (23.7pmol/L) after 4 hours [3].

In total there will be 8 study visits for participants with T1D and 1 study visit for the non-DM participants.

### **1.3 Participants Identification**

#### **1.3.1 Trial Participants**

The anticipated recruitment period is 12 months; the recruitment target is 20 participants with T1D and 10 non-DM controls. The study will aim to include participants of different age groups.

#### **1.3.2 Inclusion Criteria**

Type 1 diabetes group:

1. T1D diagnosed  $\geq 12$  months prior to screening
2. Age 18-75 years
3. Either on insulin pump or multiple daily insulin injections
4. HbA1c < 10% (86mmol/mol) at screening
5. Prior training regarding insulin dose-adjustment and management of hypoglycaemia
6. Willing and able to give informed consent for participation in the trial

- 
7. In the Investigator's opinion is able and willing to comply with all trial requirements

Non-DM control group:

1. Age 18-75 years
2. HbA1c  $\leq 6.0\%$  (42mmol/mol) at screening
3. Willing and able to give informed consent for participation in the trial
4. In the Investigator's opinion is able and willing to comply with all trial requirements

### 1.3.3 Exclusion Criteria

T1D group only:

1. An episode of diabetic ketoacidosis in the previous 1 month
2. Severe hypoglycaemia requiring third party intervention on more than 1 occasion in the preceding 12 months
3. Active diabetic retinopathy (including active proliferative diabetic retinopathy or vitreous haemorrhage in the past 6 months)

T1D and non-diabetic group:

4. Haemoglobin < 125 g/L
5. History of seizure or coma
6. Pregnancy, breast feeding or women of childbearing potential without adequate contraception
7. Renal impairment (eGFR  $\leq 50$  ml/min) at screening
8. ALT >2.5 $\times$ upper limit of the assay normal range or known liver disease, specifically bilirubin >30  $\mu$ mol/L that is associated with other evidence of liver failure.
9. Uncontrolled hypertension (>180 mmHg systolic or > 100 mmHg diastolic)
10. History of ischaemic heart disease (unless has had successful reperfusion), stroke/transient ischaemic attack (TIA), ventricular rhythm disturbances or thromboembolic disease
11. On beta-blocker medication
12. A history of heart failure (New York Heart Association, NYHA, Class 3 or 4)

- 
13. Untreated Grave's disease
  14. History of ECG or stress test findings indicating active ischaemia or a condition that would compromise the participant's safety
  15. Known history of porphyria
  16. Concomitant use of bosentan
  17. Known or suspected allergy to the trial product or related products
  18. Have received any investigational drug within 3 months prior to screening
  19. Systemic (i.e. other than topical) corticosteroid treatment within 30 days prior to the start or at any time during the trial period
  20. Major psychiatric disease including eating disorders, history of drug and alcohol abuse
  21. Known malignancy or any other condition or circumstance which, in the opinion of the investigator, would affect the participant's ability to participate in the protocol

It is worth noting that although the SmPC of both Amiglida (glibenclamide) and Forxiga (Dapagliflozin) present an extensive list of medications which might interact with these drugs, given the low dosage administration, the limited number of times that participants are required to administer these medications, as well as the different study population investigated, these interactions are not considered clinically relevant and will not form part of the exclusion criteria.

### **1.3.4 Sample Size Determination**

There are currently no data on plasma glucagon levels from human trials using low-dose sulfonylureas in patients with type 1 diabetes. The sample size calculations are based on the data generated from the LEGEND-A trial [4] (NCT02830048 - completed) and interim analysis from the DEPTH trial (NCT03537131 – suspended due to the COVID-19 pandemic).

The LEGEND-A trial suggested glibenclamide (at a dose of 0.3mg/day) could change plasma glucagon levels in participants with type 2 diabetes by 30% (magnitude of effect), while the DEPTH trial suggested that participants with type 1 diabetes who experienced exercise-induced hypoglycaemia had mean plasma glucagon values of 5.54pmol/L (SD 2.14pmol/L) at the time of hypoglycaemia (defined as <3.3mmol/L).

For the non-diabetic control group, data from a clinical study in healthy volunteers [5], which used similar methodology and a plasma glucagon assay comparable to the one we will use in our trial, demonstrated that the mean plasma glucagon values during the hypoglycaemia plateau of 23.3 pmol/L (SD 5.7pmol/L).

These figures indicate that 20 participants with T1D, and 10 participants without diabetes (including 5% dropout) would give the LEGEND-D trial 80% power to detect a 30% increase in plasma glucagon levels (the primary endpoint) during induced hypoglycaemia (hyperinsulinaemic-hypoglycaemic clamp).

#### 1.4 Schedule of Study Assessments

Individual participant's involvement: T1D group = maximum 77 days, including 8 days washout non-DM group = 1 day. Trial duration: 11 months

Trial start date: 15 August 2023

Trial End Date: 30 May 2025

Estimated recruitment dates: August'23 – 30 November 2024

#### 1.5 Changes to the Planned Analysis

No intended changes to planned analysis.

## 2 Endpoints

### 2.1 Primary Endpoints

#### 2.1.1 Definition and Derivation of Primary Endpoint(s)

The primary endpoint in this study is the difference in plasma glucagon response during induced hypoglycaemia and baseline (pre-treatment). It is defined as the concentration of plasma glucagon measured in pmol/L at 40min during the hypoglycaemic phase of the hyper-insulinaemic hypoglycaemic clamp, at baseline and at each dose step i.e. 0.3mg, 0.6mg or 3mg of glibenclamide (T1D group only).

#### 2.1.2 Primary Hypothesis under Investigation

The hypothesis to be tested for the primary analysis is given below:

$H_0$ : There is no difference in counter-regulatory plasma glucagon concentration (pmol/L) during induced hypoglycaemia compared to baseline (pre-treatment) in people randomised to glibenclamide at 0.3mg, 0.6mg or 3mg (**Table 3**) daily for 14-18 days.

### 2.1.3 Stopping Rules

The trial will be terminated if there are serious adverse events that occur in three or more (>10%) of participants.

### 2.1.4 Handling of Missing Data

Any missing data regarding blood results will be checked with the corresponding labs (Oxford University Hospitals NHS Foundation Trust or University of Oxford). The same will apply to spurious data. If two or more data points for the primary outcome (glucagon concentration) are missing from the same participant (excluding the baseline hypo clamp, which is essential), then the participant will be withdrawn from the trial.

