### 2.2.3 Handling of Missing Data

All missing data will be handled as detailed in 2.1.4.

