### **3.2 Intent-to-treat Population / Full analysis set**

The intention to treat population (ITT) is defined as the set of all randomised patients. Any patient found to have followed a sequence that is different from that to which they were randomised will be counted in the sequence to which they were randomised. Hence, data from all randomised participants will be included in the analysis.

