## **5 Statistical Methodology**

The statistical methodology for the main primary analysis is described below. Analyses will use the ITT population (section 3.2) for primary and exploratory endpoint(s), and safety population for safety endpoint(s). All statistical significance will be assessed using

an alpha value of 0.05 (95% confidence interval). The summary statistics and statistical estimates will be presented with one decimal place unless more decimal places are needed to interpret the data. All p-values will be rounded to 3 decimal places. All Tables and Figures documented in this SAP are shell versions of the anticipated results and output formats of the analyses to be conducted for the study.

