## 5.3 Primary Endpoint Analysis

### 5.3.1 Primary Efficacy Analysis

To determine whether people randomised to glibenclamide at 0.3mg, 0.6mg or 3mg daily for 14-18 days can change the counter-regulatory plasma glucagon concentration measured in pmol/L at 40min during induced hypoglycaemia compared to baseline (pre-treatment) in T1D group only. We will use 3 separate paired t-tests to compare plasma glucagon concentration (pmol/L) at baseline and at each glibenclamide dose step i.e. 0mg vs 0.3mg, 0mg vs 0.6mg, and 0mg vs 3mg. We will also use linear random effects model [6] using plasma glucagon concentration (pmol/L) at each glibenclamide dose step as dependent variable and including treatment, period, and sequence of treatment to account for within-subject correlation to quantify the magnitude and direction of the change (increase/decrease). We will also adjust for age, gender, body weight, height, SBP, DBP and resting heart rate.

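### The rule that withdraws a participant with two missing dose-step glucagon values is not reconciled with the all-randomised analysis set, and loses data on either reading

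*SAP*

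**What the plan says.** Section 2.1.4 is the SAP's only missing-data rule. Missing or spurious blood results are first checked with the laboratory. Then: "If two or more data points for the primary outcome (glucagon concentration) are missing from the same participant", leaving aside the baseline clamp, "then the participant will be withdrawn from the trial". Section 2.2.3 carries this over to the exploratory endpoints: "All missing data will be handled as detailed in 2.1.4".

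Section 3.2 reads: "The intention to treat population (ITT) is defined as the set of all randomised patients". It concludes: "Hence, data from all randomised participants will be included in the analysis". Section 5 assigns this population to both the primary and the exploratory endpoints, and uses a separate safety population for safety.

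Under 2.1.1 the primary outcome is the 40-minute glucagon value in the hypoglycaemic phase, once at baseline and once at each of three glibenclamide doses. The analysis in 5.3.1 is: "We will use 3 separate paired t-tests to compare plasma glucagon concentration (pmol/L) at baseline and at each glibenclamide dose step". A linear random effects model with treatment, period and sequence is also planned. Sections 5.3.2 and 5.4.2 plan no sensitivity analysis.

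**The concern.** The rule stands under a missing-data heading, so an analyst will look to it for who is analysed. It answers in terms of trial participation, while 3.2 and 5 answer in terms of the analysis set, and nothing connects the two. One analyst could drop a withdrawn participant's values and another could keep them, and both could cite the SAP.

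Neither planned method needs the rule. Each paired test needs only the baseline and one dose value, and the random effects model accepts incomplete records. If the rule does exclude people, inclusion depends on events after randomisation, such as a failed assay or an incomplete clamp, and no planned analysis would show the effect.

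**Working it through.** **1. What triggers the rule.** There is one primary-outcome value per clamp and baseline is not counted. The rule therefore counts at most three values per participant and fires when two or three are missing. One missing dose step is tolerated, so those retained have at least two of three dose steps.

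**2. The two readings.**

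- *Excluded from analysis.* With exactly two dose steps missing, the participant still has one complete baseline-dose pair, which is lost together with their exploratory data. With all three missing there is no pair to lose.
- *Participation stops, data kept.* If the first two dose steps are missing, the third dose clamp and the dapagliflozin clamp are not done. If the second missing value falls at the third step, only the dapagliflozin clamp is lost. If missing values come to light only after the last visit, stopping participation has no effect and exclusion is the only meaning left.

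**3. How often.** The SAP gives no missingness rate. Assume each dose step is missing with probability q, independently, in 20 participants (60 baseline-dose pairs).

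- P(exactly two missing) = 3q²(1−q)
- P(rule fires) = 3q²(1−q) + q³
- Expected withdrawals = 20 × P(rule fires)
- Pairs lost under exclusion = 20 × 3q²(1−q)
- Pairs lost if participation stops = 20 × q²(1−q), the case where the first two steps are missing and the third would have been observed
- P(at least one withdrawal) = 1 − (1 − P(rule fires))²⁰

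| q | P(rule fires) | Withdrawn of 20 | Pairs lost of 60, exclusion | Pairs lost of 60, participation stops | P(at least one) |
|---|---|---|---|---|---|
| 0.05 | 0.0071 + 0.0001 = 0.0073 | 0.15 | 0.14 | 0.05 | 0.135 |
| 0.10 | 0.027 + 0.001 = 0.028 | 0.56 | 0.54 | 0.18 | 0.433 |
| 0.20 | 0.096 + 0.008 = 0.104 | 2.08 | 1.92 | 0.64 | 0.889 |

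**4. Power.** Section 1.3.4 states 80% power with 20 T1D participants including 5% dropout, for a 30% increase from a mean of 5.54 pmol/L (SD 2.14). The difference is 0.30 × 5.54 = 1.662 pmol/L. The SD of the paired difference is not given, so the stated figure can be matched but not confirmed. With within-subject correlation ρ, SD of difference = 2.14 × √(2(1−ρ)). At ρ = 0.35 this is 2.44, a paired t-test (two-sided 0.05, noncentral t) needs n = 19, and 19/0.95 = 20. At ρ = 0.5 the SD of difference is 2.14.

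| Pairs in one dose comparison | Power, SD of difference 2.14 | Power, SD of difference 2.44 |
|---|---|---|
| 19 | 0.893 | 0.802 |
| 18 | 0.874 | 0.777 |
| 17 | 0.852 | 0.751 |

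Each lost pair belongs to one of the three comparisons. Moving down two rows needs two removed participants whose surviving pair is at the same dose. The 5% dropout allowance may already cover one of them.

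**5. Bias.** This is an illustrative simulation for one dose comparison. It assumes a true mean change of 1.66, between-subject and residual SDs of 1.5, and a higher chance of a missing step in participants with a smaller change.

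| Relation of missingness to response | Missing per step | Mean change, all available pairs | Mean change, rule used as exclusion |
|---|---|---|---|
| None | 15.5% | 1.665 | 1.665 |
| Moderate | 16.5% | 1.783 | 1.817 |
| Strong | 19.3% | 1.913 | 1.990 |

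The rule adds 1.817 − 1.783 = 0.034 and 1.990 − 1.913 = 0.077 pmol/L in the last two rows, and nothing in the first.

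**The case against.** The strongest reply is that there is no contradiction. Section 2.1.4 speaks of withdrawal from the trial, not of deleting data or leaving an analysis set. Read with 3.2 and 5, participation stops and the collected values stay in. That stands as a possible reading, and it is why the point is a failure to reconcile the sections. It does not clear the rule, because on that reading later clamps can be lost, and the rule's heading and its extension by 2.2.3 make exclusion just as natural.

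A reader might infer three stronger things that the document does not support:

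- *The rule yields a completer analysis.* It does not. A participant with two of three dose steps is kept.
- *Adverse-event data are removed.* This is not shown. Safety uses its own population (3.4 and 5), and nothing in 2.1.4 takes recorded events out of it.
- *The loss of power or the bias is serious.* At 5 to 10% missing per step, fewer than one participant is expected to trigger the rule. In the simulation most of the bias is already present when all available pairs are used, so dropping the rule would not remove it.

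The missing protocol may also govern withdrawal from visits. That is a reason to reconcile the two documents, but it does not settle which data the SAP analyses.

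**Conclusion.** The point holds as an unreconciled and counterproductive rule that should be fixed. The gap between 2.1.4 with 2.2.3 and 3.2 with 5 exists at any missingness rate, and each reading loses information that the planned analyses could use. The numerical effect is small at 5 to 10% missing per step and becomes material from about 15 to 20%. At 20%, about two of 20 participants would be withdrawn and 1.9 of 60 pairs lost under exclusion. These figures rest on independent missingness at assumed rates, and the power figures on an assumed SD of the paired difference. The size of any bias cannot be fixed from the SAP. It arises from the rule only if missingness is related to response.

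**What to change.** Replace the withdrawal sentence in 2.1.4 with: *No participant is removed from the analysis because of missing values; all observed clamps of all randomised T1D participants enter the random effects model, and each paired comparison uses every available baseline-dose pair.*

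Delete 2.2.3 or reword it to match. Add one comparison of the primary estimate with that from participants who have all four clamps (baseline and three doses).

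Whether a participant continues study visits is not for the missing-data section to decide. That part of 2.1.4 must be reconciled with the protocol's withdrawal criteria.

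The cost is a change of SAP wording and slightly more analysis. The model will rely on values being missing at random, which the SAP should say. The available-pairs tests remain open to bias if missingness depends on response.
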